#### Depression and Anxiety in Stroke Survivors

Psychological and affective disorders often occur after a stroke. The most common are depressive and anxious symptoms. Prevalence of depression ranges from approximately 20 to 40% (Barkercollo, 2007; De Wit et al., 2008; Ayerbe et al., 2011, 2013) and prevalence of anxiety is estimated between 18 and 32% in general stroke survivors’ population (Barkercollo, 2007; Ayerbe et al., 2014; Schöttke and Giabbiconi, 2015).

Several studies focused on depression after a stroke. In comparison, very few studies have been published considering specifically minor stroke patients while the prevalence of depression has been estimated at the same rates than in general stroke survivors populations (Altieri et al., 2012; Shi et al., 2015).

Not only it appears essential to identify and to treat post-stroke depression (PSD) and post-stroke-anxiety (PSA) because of their symptoms burden but also because of their negative impact on functional outcomes and mortality after stroke (Chemerinski et al., 2001; Naess et al., 2010; Bartoli et al., 2013).

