#### Sample Size

Forty participants will be included in the study. According to previous research using EMA for psychological assessment, an acceptance rate between 75 and 90% is expected (Johnson et al., 2009a,b). Thus, we expect data from 30 to 36 participants to perform analysis.

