##### Other measures

###### Sociodemographic information

Including gender, age, marital status, familial situation at home (alone, spouse, child, etc), academic level, and socioeconomic status are collected or during the first interview either from the medical records.

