###### Stroke characteristics and functional deficit

Stroke localization (right or left hemisphere) and type (ischemic or hemorrhagic) based on medical imageries and exams conclusions. In case of ischemic stroke, we record if patients have received a thrombolytic treatment. Functional deficit is assessed with the National Institutes of Health Stroke Scale (NIHSS). This scale is administered by a trained health professional (physicians, nurses) and is composed of 15 items measuring neurological motor and cognitive deficits after a stroke. Items are related to consciousness, cognition, inattention, speech, sensory and motor functioning, visual fields functioning and ataxia (Meyer and Lyden, 2009; Zandieh et al., 2012).

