##### Outcomes and statistical methods for secondary objectives

(1) Frequency will be estimated as the ratio of depressed and anxious participants to the total number of participants. Presence of depression and anxiety will be determined in two different ways: according to the examination of psychiatric disorders during the semi-structured interview; and as a function of the cut-off scores of self-reported questionnaires and clinicians’ ratings scale previously reported in the instruments section.

(2) Univariate logistic regression analysis will be performed to study if the clinical variables (subtypes of anxiety and depression symptoms, coping strategies) predict depression and anxiety within each time and between times of the study.

(3) Descriptive analysis will be performed on clinical, sociodemographic and medical measures to describe depressed and anxious participants. Their results will be compared to healthy participants (presenting no significant depression and anxiety) with Chi-square and Student’s *t*-test.

(4) We will examine whether EMA of the different symptoms of depression and anxiety are associated with self-report and clinician-rated depression and anxiety to describe characteristics of PSD and PSA. Means-as-outcomes modeling will be used to describe those associations.

(5) In order to describe the time dynamics between anxiety and depression symptoms, coping strategies and contextual settings assessed with EMA, we will use a Multilevel Vector Autoregressive method (Bringmann et al., 2013). With the Vector Autoregressive (VAR) model, each variable at time point *t* is regressed to the time point *t* – 1 of every other variable. For example, sadness at 1 pm is regressed with all other depression and anxiety symptoms (including sadness) at 10 am. The multilevel-VAR model is suited to the hierarchical structure of EMA data and it enables to describe population dynamics as a function of within-person variability.

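### Chi-square is fixed for comparing a small case group with healthy participants; if cases are about 20% or less of those compared, one carrier of a rare feature can give an uncorrected p below 0.05

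*Protocol article*

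**What the plan says.** In the Protocol article, Outcomes and statistical methods for secondary objectives, item (3) describes depressed and anxious participants on clinical, sociodemographic and medical measures. It then states: "Their results will be compared to healthy participants (presenting no significant depression and anxiety) with Chi-square", with Student's t-test as the companion method. Healthy means free of both disorders. The article gives no significance level and does not say whether a continuity correction applies.

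The numbers available come from three places:

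- **Sample Size:** "Forty participants will be included in the study", "an acceptance rate between 75 and 90% is expected", and hence "we expect data from 30 to 36 participants to perform analysis".
- **Depression and Anxiety in Stroke Survivors:** depression at roughly 20 to 40%, and "prevalence of anxiety is estimated between 18 and 32% in general stroke" survivors. Anticipated Results expects frequencies in minor stroke to be as high.
- **Limitations:** patients who refuse the smartphone part stay in the general study with the same questionnaires and interviews. Comparisons that need no smartphone data can therefore use up to all 40.

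The characteristics to be compared include some with several categories, "Including gender, age, marital status, familial situation at home (alone, spouse, child, etc), academic level, and socioeconomic status", and some that may be unevenly split, such as stroke "type (ischemic or hemorrhagic) based on medical imageries and exams conclusions" and thrombolytic treatment. No frequencies are given for them.

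**The concern.** The Chi-square p-value is a large-sample approximation that becomes unreliable when expected cell counts are small. Here the case group is small by the article's own figures, and some characteristics may be rare. Objective 3 is meant to say which characteristics go with depression and anxiety after minor stroke. If the named test is applied literally, a feature seen in one patient could be reported as distinguishing cases from healthy participants, although chance alone would put that patient among the cases about one time in five or six.

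**Working it through.** **1. The plan's own figure.** 40 × 0.75 = 30 and 40 × 0.90 = 36, which reproduces the stated 30 to 36.

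**2. Number of cases.** The lowest prevalence quoted is 18% (anxiety) and the highest 40% (depression).

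- Among 30 to 36: 30 × 0.18 = 5.4 and 36 × 0.40 = 14.4, so about 5 to 14.
- Among all 40: 40 × 0.18 = 7.2 and 40 × 0.40 = 16, so about 7 to 16.

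**3. Expected counts.** In the case row, the expected count is the number of cases times the category's share. Reaching 5 needs a share of 5/5 = 100% with 5 cases, 5/7 = 71% with 7, 5/14 = 36% with 14 and 5/16 = 31% with 16. Uncommon categories fall below 5 across the whole range.

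**4. One carrier, who is a case.** With N compared, n1 cases and n0 healthy, the uncorrected statistic is X² = [N/(N − 1)] × (n0/n1) on 1 degree of freedom. For 5 cases and 25 healthy, X² = (30/29) × (25/5) = 5.17, p = 0.023. The exact p is n1/N = 5/30 = 0.167.

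| Cases v healthy | Uncorrected Chi-square p | Fisher p |
|---|---|---|
| 5 v 25 | 0.023 | 0.167 |
| 6 v 24 | 0.042 | 0.200 |
| 7 v 23 | 0.065 | 0.233 |
| 6 v 30 | 0.023 | 0.167 |
| 7 v 29 | 0.039 | 0.194 |
| 8 v 28 | 0.058 | 0.222 |
| 7 v 33 | 0.028 | 0.175 |
| 8 v 32 | 0.043 | 0.200 |
| 9 v 31 | 0.060 | 0.225 |
| 12 v 18 | 0.213 | 0.400 |
| 14 v 22 | 0.204 | 0.389 |
| 16 v 24 | 0.215 | 0.400 |

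The statistic passes 3.84 only when n1/N is at or below about 0.21. With the continuity correction, the tables that cross 0.05 give p of 0.36 to 0.45 instead.

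**5. Overlap of the two disorders.** The table sets healthy = N − cases, so it assumes nobody has only the other disorder. With 5 anxious and 6 depressed among 30 and no overlap, healthy = 30 − 11 = 19:

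- anxious v healthy (5 v 19): p = 0.046
- depressed v healthy (6 v 19): p = 0.069
- pooled (11 v 19): p = 0.181

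**6. True level of the nominal 5% test.** Binomial probabilities were summed over all 2×2 tables with p < 0.05, with the same feature frequency in both groups. The feature frequencies are assumptions.

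| Setting | Feature frequency | Uncorrected Chi-square | Fisher |
|---|---|---|---|
| 5 to 8 cases (5 v 25 up to 8 v 32) | 3–5% | 6.9–9.0% | 0.4–1.5% |
| 5 to 8 cases | 15–50% | 3.2–5.8% | 1.6–3.2% |
| 12 v 18, 14 v 22, 16 v 24 | 3–5% | 0.3–1.3% | at most 0.2% |
| 12 v 18, 14 v 22, 16 v 24 | 15–50% | 3.6–6.2% | 1.3–3.5% |

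**The case against.** The strongest reply is that this is a one-sentence summary in a condensed article, and that a small-cell fallback belongs in the full protocol or analysis plan, which is not shown. That stands against any complaint that an exact test is missing. It does not dispose of the point, because the article names a test, and that test taken literally misleads in sparse tables.

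A reader might infer that one patient can produce significance anywhere in the range of 5 to 14 cases. The figures do not support that: the effect is gone at 7 of 30, 8 of 36 and 9 of 40, and p is about 0.2 at 12 to 16 cases. Most of the quoted prevalence range lies above the threshold, and low overlap between the disorders narrows the window further.

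A reader might also infer that any expected count below 5 invalidates the test. With fewer than 10 cases even an evenly split feature has such a count, yet for features carried by 15 to 50% of patients the true level is about 3 to 6%.

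Three further points are fair. The 0.05 level and the uncorrected form are assumptions. No passage supports a frequency of 3 to 5% for any listed variable. And Fisher's test misses the nominal level too, on the conservative side: 0.4 to 1.5% for rare features, much like the continuity-corrected Chi-square at 0.4 to 1.3%.

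**Conclusion.** The point holds in a limited form. At the low end of the article's prevalence range, with about 5 to 8 cases making up about 20% or less of those compared, uncorrected Chi-square can turn a single carrier into p = 0.02 to 0.04 where the exact p is 0.17 to 0.20. Its true level is about 7 to 9% for a feature assumed to occur in 3 to 5% of patients. This rests on the uncorrected statistic, a 0.05 threshold and substantial overlap between the two disorders (or, for anxiety alone, a case share still near 20%). Outside those conditions Chi-square is close to nominal or conservative.

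Severity is minor. The comparison is secondary and descriptive, and the primary feasibility and validity analyses do not use it.

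**What to change.** In item (3) of the secondary analyses, state that categorical characteristics are compared with Fisher's exact test (Fisher-Freeman-Halton for more than two categories), preferably in mid-p form, where any expected count is below 5, and with Chi-square otherwise. Show the counts in each group beside every p-value, so that a result resting on one or two patients is visible.

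The cost is one line of wording, with no new data or patients. The downside is conservatism for rare features under ordinary Fisher, as shown above. Mid-p eases this: in the one-carrier tables that cross 0.05 it halves the exact p, to 0.167/2 = 0.083 up to 0.200/2 = 0.100, still not significant. In exchange, its true level can slightly exceed 5%, with a maximum of about 6% over the group sizes examined.

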## Discussion

### Anticipated Results

#### Primary Objective

A participation rate at inclusion between 75 and 90% is expected regarding previous results with EMA method (Johnson et al., 2009a,b). The completion rate of EMA questionnaires is expected to be at least of 80% for the entire group during each phase (Sibon et al., 2012). In order to have satisfying validity, correlations between EMA indexes and data collected using other methods are expected to be higher than 0.70.

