#### Limits of Previous Studies and Perspectives for Further Research

The large majority of studies presented earlier are based on designs resorting to classical standard measures of depressive and anxious symptoms and coping strategies. But those conventional methods have been controversial because of recall biases implied by retrospective self-report assessments (Smyth and Stone, 2003). One question should be raised concerning the ecological validity of previous findings and models concerning PSD and PSA based on classical methods: is it what happens in real life? Does it reflect the real contextually and temporally dynamics of the processes and evolution of depression, anxiety and coping after a stroke?

The Ecological Momentary Assessment (EMA) is a methodological approach which aims to be specifically designed for the purpose of measuring phenomenon in their real specific ecological context of appearance. Based on the immediate or short term description of a phenomenon, EMA allows to study behaviors in their real daily life environment while limiting recall biases (Shiffman et al., 2008; Ebner-Priemer and Trull, 2009). Thus, EMA allows to study theoretical models in psychopathology by observing dynamic processes between multiple emotional, behavioral and cognitive phenomenon directly in their real context of appearance (Carpenter et al., 2016).

Ecological Momentary Assessment has been developed in the past three decades in the context of psychological and behavioral research for many conditions such as depression (Wenze and Miller, 2010; aan het Rot et al., 2012; Telford et al., 2012), anxiety (Walz et al., 2014), substance use (Shiffman, 2009; Morgenstern et al., 2014; Serre et al., 2015) or somatic diseases (Finan et al., 2008; Sibon et al., 2012; Bring et al., 2013; Kim et al., 2016).

There are still few studies reporting psychological EMA of stroke populations and all of those studies exclusively focused on depression (Lassalle-Lagadec et al., 2012; Sibon et al., 2012; Jean et al., 2013; Mazure et al., 2014). Previous results showed that the different daily symptoms of depression after stroke have specific evolution: somatic symptoms are less lasting than emotional and cognitive ones (Sibon et al., 2012). Depression was also related to specific daily life behaviors (Jean et al., 2013) and emotional reactivity to daily positive and negative events after stroke (Mazure et al., 2014).

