#### Data Analysis

##### Outcomes and statistical methods for primary objectives

Feasibility and acceptability of the EMA method will be assessed by examination of acceptance and compliance rate, fatigue effects and reactivity to assessment: completion rate during each week, participation at follow-up weeks (phases 2 and 3), missing data and assessment duration across time during each phase. Descriptive analysis will be performed to describe feasibility and acceptability. Compliance will be assessed as the completion rate of EMA questionnaires. This rate will be calculated as the ratio of completed questionnaires to all sent questionnaires within each phase (four questionnaires per day during 7 days for each participant). Follow-up participation will be the ratio of number of participants at phase 2 and 3 to the number of participants at inclusion (phase 1). Fatigue effect will be calculated as the evolution of the within-day mean of missing data. Reactivity to EMA assessment will be estimated by comparing anxiety, depression and quality of life scores (self-reported questionnaires and clinicians’ ratings) of EMA participants to other participants (not involved in the EMA part of the study, more information is given in the limitations section below).

Validity of the method will be examined by using three different EMA indexes consisting in different aggregation of anxious and depressive symptoms assessed with EMA for each participant: a global anxiety and depression index (including all 11 symptoms assessed), a specific depression index (including sadness, anhedonia, fatigue, concentration difficulties, negative thoughts, pessimism) and a specific anxiety index (including anxiety, agitation, physical tension, irritability, concentration difficulties).

Validity will be assessed by using Pearson correlations between EMA indexes with self-reported questionnaires’ scores and clinicians’ ratings. Only participants with a satisfying minimum within- and between-day compliance will be included in this analysis (i.e., at least 5 EMA questionnaires filled). We will observe associations between: the global EMA index and the overall score of the HADS; the depression EMA index with the BDI score, the HADS depression subscale score and the MADRS score; the anxiety EMA index with the HADS anxiety subscale score and the HAM-A.

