### Research and Clinical Implications

#### Research Implications

Ecological Momentary Assessment using smartphone application is a wide area in terms of research perspectives. The great ecological validity of instantaneous capture of phenomenon in their real life contexts makes EMA method a promising perspective for research and knowledge in the field of psychopathology.

However, standard instruments still have to be developed. Recent published papers in different fields of psychology may be pieces of evidence that solid references are needed and that sharing protocols could help (Benarous et al., 2016; Mareva et al., 2016). We hopefully think that sharing and presenting the innovative protocol of the present work will contribute to develop EMA research. We expect this study to participate in the development of EMA research and methods in the area of psychological processes and more accurately in the study of populations with somatic and neurologic conditions.

The fact that we combined different assessment methods of psychopathology (i.e., self-report questionnaires, clinicians’ observation, EMA) is a main strength of this study. Indeed, the results will bring information regarding the validity of these different methods of psychological assessment.

Finally, the longitudinal EMA design of the study with three distinct phases at different times over a 4-month period is an original design for which feasibility has still to be informed.

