#### Clinical Implications

Concerning the acute case of PSD and PSA etiopathogenesis, EMA research offers promising results so as to better understand the determinants, characteristics and the evolution of those emotional manifestations after a minor stroke. The EMA design of this study will help to clarify the biopsychosocial model of PSD and PSA (Aben and Verhey, 2006; Mast and Vedrody, 2006). Because of its particular ecological dimension, EMA makes possible to approach psychological phenomenon in real life environment. Thus, it enables to observe processes between behaviors, thoughts, emotions and environment. Our longitudinal EMA design could offers interesting results concerning those processes at different times after stroke.

We are expecting this study to contribute in the enhancement of diagnostic accuracy of psychiatric disorders and the detection of emotional distress in minor stroke population. We hopefully think the results of the present study could lead to identify specific reliable signs of depression and anxiety at different times after a stroke. Such results could help clinicians and care providers who work with stroke patients so as to facilitate the detection of emotional disorders by recommending them to focus on specific symptoms.

Finally, the remotely assessment of depression and anxiety using a smartphone application offers interesting perspectives for home-returned cares and follow-ups. Early supported discharge should be a better option for stroke patients (Mas and Inzitari, 2015) and is the main trajectory of minor stroke patients. The results of the present study will bring information concerning feasibility, validity and reliability of smartphone application psychological assessment after hospital discharge. Considering those results, further research could be suggested so as to develop a standard instrument for depression and anxiety screening after hospital discharge of stroke patients. Previous research in breast cancer population shown promising results in the field of mobile tool for screening depression (Kim et al., 2016). It still has to be developed in stroke population and it could lead to the improvement of the early supported discharge after a stroke by taking into account a remotely psychological follow-up.

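### EMA validity is read against one unsourced correlation of 0.70, and no correlations among the conventional scales are planned to interpret it

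*Protocol article*

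**What the plan says.** The benchmark is in the Discussion of the protocol article, under Anticipated Results, Primary Objective. As the condition for validity to be satisfying, it states that "correlations between EMA indexes and data collected using other methods are expected to be higher than 0.70". The two neighbouring expectations, on participation and on completion rate, each cite a source. This one does not.

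The analysis is in Outcomes and statistical methods for primary objectives: "Validity will be assessed by using Pearson correlations between EMA indexes with self-reported questionnaires" (their scores) and with clinician ratings. Six pairs are listed:

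- one for the global index, paired with the HADS total;
- three for depression, given as "the depression EMA index with the BDI score, the HADS depression subscale score and the MADRS score";
- two for anxiety, where the EMA index is paired with HADS-A and with HAM-A.

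No pair joins two conventional scales.

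Two other places bear on how the result will be read. Limits of Previous Studies and Perspectives for Further Research motivates EMA partly because "those conventional methods have been controversial because of recall biases implied by retrospective self-report assessments". Research Implications calls the combination of methods a main strength and says that "the results will bring information regarding the validity of these different methods of psychological assessment".

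Table 1 shows the BDI-II and HADS at phases 1b, 2 and 3, and the MADRS, HAM-A and MINI at phases 1a and 3. Phase 3 is the only point at which all of them are taken.

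**The concern.** A correlation between two imperfect measures depends on the error in both. If EMA and the BDI correlate at 0.62, the shortfall from 0.70 may come from EMA, from the BDI, or from both. The usual way to tell is to see how well the established scales agree with each other in the same patients. That is not planned, so the only yardstick is an absolute value with no stated origin.

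The problem is sharper because the article expects EMA to depart from retrospective self-report. Where EMA removes recall error, some divergence from the BDI and HADS is what the rationale predicts, yet against 0.70 it would count as weaker validity.

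At stake is the validity conclusion within the primary objective: an EMA index as good as the scales could be reported as unsatisfactory. In addition, six correlations that all involve EMA give no comparison of self-report with clinician rating, although the article says it will inform on the validity of each method.

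**Working it through.** **1. The plan's own figure.** Sample Size gives 40 participants and an acceptance rate of 75 to 90%. 40 × 0.75 = 30 and 40 × 0.90 = 36, so the stated 30 to 36 reproduces. The 0.70 has no derivation to reproduce.

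**2. Count of pairs.** Self-report: global-HADS total, depression-BDI, depression-HADS-D, anxiety-HADS-A (four). Clinician-rated: depression-MADRS, anxiety-HAM-A (two). Scale with scale: none.

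**3. Expected EMA correlation for a given agreement among scales.** Assume that all measures of a domain reflect one common factor with independent errors. Let EMA have loading a and each scale loading b. Then inter-scale r = b² and EMA-scale r = a × b. An EMA as good as the scales (a = b) has expected r = b². An error-free EMA (a = 1) has expected r = b. Reaching 0.70 needs a = 0.70 / b. The article gives no inter-scale correlations, so these are shown over an assumed range:

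| Inter-scale r | EMA as good as scales | Error-free EMA | EMA loading needed for 0.70 |
|---|---|---|---|
| 0.40 | 0.40 | 0.63 | 1.11 (impossible) |
| 0.49 | 0.49 | 0.70 | 1.00 |
| 0.50 | 0.50 | 0.71 | 0.99 |
| 0.60 | 0.60 | 0.775 | 0.90 |
| 0.70 | 0.70 | 0.84 | 0.84 |
| 0.80 | 0.80 | 0.89 | 0.78 |

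At 0.60 the scales themselves have loading √0.60 = 0.775, so EMA would need 0.90, clearly better than the scales, to be expected at 0.70. At 0.80 the benchmark is easy for an equally good EMA. Its meaning thus depends on a quantity that is not planned to be estimated.

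**4. Same point through reliability.** Observed r = true r × √(rel₁ × rel₂). The true correlation needed for an observed 0.70 is:

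- both reliabilities 0.90: 0.70 / 0.90 = 0.78
- both 0.80: 0.70 / 0.80 = 0.875
- both 0.70: 0.70 / 0.70 = 1.00

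The reliabilities are assumptions.

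**5. Sampling error.** Fisher z with SE = 1/√(n − 3). For an observed r = 0.70, z = 0.867.

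- n = 30: SE 0.192, 95% CI 0.45 to 0.85
- n = 36: SE 0.174, 95% CI 0.48 to 0.84

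Chance that one observed correlation exceeds 0.70, at n = 30 / n = 36: population r 0.60, 18% / 16%; 0.70, 50% / 50%; 0.80, 89% / 91%. So an EMA that matches scales intercorrelating at 0.60 misses 0.70 on a given pair in more than 80% of samples.

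**The case against.** Several parts of the opposing case stand, and they limit the point.

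- **A reader might infer a pass rule.** The 0.70 is an expectation in the Discussion. The methods section says only that associations will be examined, does not require all six pairs to exceed 0.70, and attaches no consequence to a miss. What remains is that the sentence ties satisfying validity to that value, so it will frame the conclusion.
- **A reader might infer that the article calls all its comparators biased.** It charges retrospective self-report, which covers the BDI and HADS. It does not say this of the MADRS or HAM-A, which follow structured interview guides. Checking a new measure against both kinds is ordinary convergent validation.
- **A reader might infer that correlation is the only test of EMA, or that the MINI is unused.** Neither holds. Compliance, follow-up participation, fatigue and reactivity are also assessed. Secondary objective 1 uses the semi-structured interview to define cases, and secondary objective 4 relates EMA symptoms to self-report and clinician-rated outcomes. The MINI is absent only from the listed validity correlations.
- **A reader might infer that the methods cannot be compared.** They can, because every scale is collected at phase 3. The comparison is simply not among the listed analyses.
- **A reader might infer that 0.70 implies poor case detection.** Accuracy figures obtained by dichotomising the correlated score say nothing about MINI diagnosis, and diagnostic accuracy is not a stated objective.

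It can also be said that a matrix of scale correlations is routine content of an analysis plan not shown here. That would answer a complaint of mere omission. It does not answer the point that the article itself fixes both the list of pairs and the yardstick, and that the yardstick cannot be interpreted alone.

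**Conclusion.** The point holds in a limited form. The article reads EMA validity against one unreferenced absolute value and lists no correlation among the conventional scales, so a result below 0.70 cannot be assigned to EMA rather than to its comparator. The listed correlations also fall short of what Research Implications promises about the different methods.

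The size depends on agreement among the scales, which the article does not give. If that agreement is about 0.70 or higher, an equally good EMA is expected to reach the benchmark. If it is 0.60, it is expected to miss, and below about 0.49 even an error-free EMA is. These figures rest on a one-factor model with independent errors. They show that a good EMA could miss the benchmark, not that it will. The change is worth making because it alters what the validity result can support at almost no cost.

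**What to change.** At phase 3, in the patients who enter the EMA validity analysis, report with 95% confidence intervals the correlations BDI-MADRS, HADS-D-MADRS, BDI-HADS-D and HADS-A-HAM-A beside the six EMA correlations. State that EMA validity will be interpreted against these rather than against 0.70 alone. Either give a source for 0.70 or call it a reference value.

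Two cautions belong with the report. At phase 3 the scales are completed at the home visit and the EMA week follows, so the scales share an occasion that EMA does not. And BDI-HADS-D shares retrospective self-report, which may raise that correlation, so the self-report with clinician pairs are the more informative yardstick.

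The cost is four extra statistics on collected data. Intervals will be wide at 30 to 36 patients (step 5 of the working), and wider if follow-up is incomplete, so the comparison is one of estimation and not a test.

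A comparison of the EMA indexes with MINI status is optional and descriptive only. The EMA symptom items were adapted from the MINI, the phase 3 interview covers the two weeks before the EMA week, and cases will be few. The article's prevalence ranges for stroke survivors (20 to 40% for depression, 18 to 32% for anxiety) imply about 6 to 14 and 5 to 12 cases among 30 to 36 patients (0.20 × 30 = 6, 0.40 × 36 = 14.4; 0.18 × 30 = 5.4, 0.32 × 36 = 11.5).
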